# **STUDY SUMMARY**

| **Full study title** | Impact of **C**ardiac prehabilitation, **RE**habilitation and patient **ED**ucation on outcomes in patients undergoing first-time **AF** ablation | |
| --- | --- | --- |
| **Short study title** | **CREED AF** | |
| **Study aim** | To compare a tailored comprehensive patient education and lifestyle/Atrial Fibrillation (AF) risk factor modification programme and cardiac pre/rehabilitation (CREED AF Intervention) vs standard of care for patients with AF who are listed for all first-time AF ablation procedure (cryoballoon or radiofrequency ablation) | |
| **Study design** | Single-centre prospective randomised controlled trial. | |
| **Study participants** | Patients with AF listed for first-time AF ablation. | |
| **Study arms** | **Control arm** – AF ablation procedure (standard care) plus 30-minute education with CREED AF practitioner.  **Intervention arm** – AF ablation procedure (standard care) plus CREED AF intervention before and after AF ablation procedure. CREED AF intervention comprised of tailored cardiac education, prehabilitation (2-3 sessions/week for 6-8 weeks) and rehabilitation (2-3 sessions/week for 6-8 weeks). | |
| **Sample size** | 106 (53 in each arm) | |
| **Planned study period** | 28 months (June 2023 to September 2025) | |
| **Planned recruitment start date** | June 2023 | |
| **Planned recruitment end date** | September 2024 | |
| **Planned study end date** | September 2025 | |
|  | **Objectives** | **Outcome Measures** |
| **Primary** | To assess the effectiveness of comprehensive cardiac prehabilitation, rehabilitation and patient education to improve exercise capacity of AF patients undergoing first-time AF ablation, compared with standard care. | VO_2peak_ measured from cardiopulmonary exercise testing (CPET) at baseline and 10 weeks (±2 weeks) post AF ablation between the standard care and intervention arms. |
| **Secondary** | To explore if CREED AF intervention can improve quality of life (QoL) in AF patients undergoing ablation. | 1. EQ-5D-5L questionnaire 2. Generic QoL questionnaire (SF-36 QoL scale) 3. Disease specific questionnaire (Atrial Fibrillation Effect on Quality-of-Life (AFEQT) |
|  | To assess cost effectiveness of the CREED AF intervention compared with standard care. | Incremental cost per quality adjusted life year (QALY). |
|  | To explore if CREED AF intervention has an impact on the short- and long-term recurrence of AF post-ablation and the need for redo-AF ablation. | AF recurrence and burden from data collected from a 1–7-day(s) cardiac Holter monitoring at 10 weeks (±2 weeks) and 12 months (±4 weeks) post ablation, and requirement for redo-AF ablation as documented in medical records reviewed at 12 months post-ablation. |
|  | To explore the impact of CREED AF intervention on relevant major adverse cardiovascular events (MACE) in AF patients. | MACE at 12 months post-ablation, defined as:   1. Hospital admission related to AF 2. Non-fatal myocardial infarction 3. Non-fatal stroke 4. Cardiovascular death 5. All-cause mortality |

Key Words: **AF ablation, Pulmonary vein isolation, VO2peak**

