# **SCHEDULE OF EVENTS**

*Table 1: Schedule of Events*

| **Procedure** | **Pre-Screening/ Lead-In Period** | **Consent & Baseline** | **Pre-Ablation Intervention** | **AF Ablation Procedure*** | **Rest** | **Post-Ablation Intervention** | **Follow-Up & Outcome Measure** | **Follow-Up** |
| --- | --- | --- | --- | --- | --- | --- | --- | --- |
|  | **Month -4 to Month -1** | **Week -2 to Day 1** | **Up to Week 8** | **Week 9 (Day 1 Ablation)** | **Up to Week 11 (2 weeks post-ablation)** | **Up to Week 19 (Up to week 10 post-ablation)** | **Up to Week 21 (Up to week 12 post-ablation)** | **Month 12 (±4weeks) post ablation** |
| Screening | X |  |  |  |  |  |  |  |
| Eligibility assessment | X |  |  |  |  |  |  |  |
| Re-Confirm Eligibility |  | X |  |  |  |  |  |  |
| Informed consent |  | X |  |  |  |  |  |  |
| Questionnaire completion (EQ-5D, SF-36, AFEQT) |  | X |  | X |  |  | X | X |
| Resource Use Questionnaire |  |  |  | X |  |  | X | X |
| Demographic data (Year of birth, sex, ethnicity, height, and weight) |  | X |  |  |  |  |  |  |
| Smoking and diet history |  | X |  |  |  |  |  |  |
| Relevant clinical history |  | X |  |  |  |  |  |  |
| Current medications |  | X |  |  |  |  |  |  |
| Standard blood tests* |  | X |  |  |  |  |  |  |
| Cardiopulmonary exercise testing |  | X |  |  |  |  | X |  |
| Randomisation |  | X |  |  |  |  |  |  |
| 1-to-1 behavioural & motivational education sessions |  |  | X^1^ |  |  | X^1^ |  |  |
| 30-minute AF risk factor modification education session |  |  | X^2^ |  |  |  |  |  |
| AF Ablation* |  |  |  | X |  |  |  |  |
| Cardiopulmonary exercise sessions for intervention arm |  |  | X |  |  | X |  |  |
| Adverse Event Reporting |  | X | X | X | X | X | X | X |
| 1–7-day(s) Holter monitor |  |  |  |  |  |  | X | X |
| Primary Outcome Analysis |  |  |  |  |  |  | X |  |
| Review of hospital records (MACE, need for redo-AF ablation, etc.) |  |  |  |  |  |  |  | X |

** Part of Standard Care*

*X^1^ 1-to-1 behavioural & motivational education session alternating weeks for 6-8 weeks pre- and post-ablation only occurring in the intervention arm*

*X^2^ one off 30-minute education session activity only occurring in the control arm*

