| To explore if the CREED AF intervention improves short- and long-term Atrial Fibrillation Effect on Quality-of-Life (AFEQT) in AF patients listed for first-time AF ablation compared to standard care. | The AFEQT is an AF-specific health-related QOL made up of 3 subscales (symptoms, daily activities, and treatment concern). The transformed overall score ranges from 0 (complete disability) to 100 (no disability).  Short-term: change of AFEQT from baseline to 10 weeks post-ablation.  Long-term: change of AFEQT from baseline to 12 months post-ablation. |
| To explore the cost-effectiveness of the CREED AF intervention compared to standard care. | The incremental cost per quality adjusted life year (QALY) will be estimated. See details in Section 10.7. |
| To explore if the CREED AF intervention can decrease AF burden and recurrences following AF ablation, and reduce the requirement for redo-AF ablation. This will be assessed with a 1–7-day cardiac Holter monitor at 10 weeks (±2 weeks) and 12-months (±4 weeks) post ablation, and on review of patients’ medical records at 12-months. | Participants will be fitted with a Holter monitor at the 10-week and 12-month post-ablation follow-ups. Of the list of summary data over the time period it is worn by the participant, only the significant AF event and burden, and when it occurred will be recorded. |
| To explore if the CREED AF intervention has an impact on major adverse cardiovascular events (MACE) at the 12-month follow-up between both groups. MACE will be defined as individual outcomes and as a composite of hospital admission related to AF, non-fatal myocardial infarction, non-fatal stroke, cardiovascular death, and all-cause mortality. | Any occurrence of the following events:   - Hospital admission related to AF (from hospital records) - Non-fatal myocardial infarction (as above) - Any non-fatal stroke (as above) - Cardiovascular death (as above) - All-cause mortality (as above)   and when each occurred. |

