The 1-to-1 education sessions in the CREED AF Intervention arm will be conducted by an exercise practitioner/researcher and will be performed either online, over the phone, or in-person. The sessions will incorporate comprehensive behavioural change and motivational strategies to improve patient adherence and compliance to risk factor modification with the aim of improving both short- and long-term adherence to exercise and lifestyle modification goals and reduce their exposure to lifestyle risk factors (e.g., smoking, alcohol consumption, weight reduction etc.). This will be guided by a participant workbook, and further sign-posting to support groups will be in accordance to individual participant’s requirements. A full compliance of education sessions is at least 2 sessions (of a total of 3; 66.7%) at each prehabilitation and rehabilitation intervention.

- 1. **Follow-up data**

In addition to cardiopulmonary exercise testing at 10 weeks follow-up post-ablation, all patients will also repeat the baseline questionnaires to assess their HRQoL, including the EQ-5D-5L, SF-36 and AFEQT, at significant intervals of the intervention journey (as outlined in the Schedule of Events). To assess for AF recurrence and burden, 7-day Holter ECG monitoring will be placed on patients at the 10 weeks and 12 months post-ablation follow-up appointments. The 10-week (±2 week) period will be seen as equivalent to a 3-month blanking period that is normally considered post-ablation in which presence of AF is not seen as a recurrence. The definition of an AF recurrence post-ablation will be an arrhythmia with the characteristics of AF that is either captured on a 12-lead ECG or documented to last for at least 30 seconds on ECG monitoring (1). At 12 months post-ablation, a retrospective review of medical records will be completed to collect data for study defined MACE. This will include, but will not be limited to, a review of clinic letters, medical coding, and A&E records.

- 1. **End of Study Definition**

The end of study definition will be when the last participant has completed their 12-month follow-up appointment and data collection post-ablation.

- 1. **Assessment and Management of Risk**

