All the scoring of HRQoL (EQ-5D-5L, SF-36 and AFEQT) will be computed as per the instrument algorithm. The scores will then be summarised descriptively overall and by treatment arms at baseline and the short- and long-term follow-up time points. The change of HRQoL from baseline to 10-week, from baseline to 12-month post-ablation, and the difference between treatment arms will be estimated with their associated 95% confidence intervals (CIs). We may explore the longitudinal effect of long-term HRQoL (12-month post-ablation). Proportion of significant AF event by treatment arms will be estimated with associated 95% CI using Kaplan-Meier. Similarly, the proportion of individual and composite MACE and its associated 95% CI by treatment arms will be estimated. The recurrence of AF burden from the Holter and each of the MACE occurrence will also be estimated by treatment arms as a time-to-event estimand. We will also perform a subgroup analysis by types of AF (persistent and paroxysmal AF) for all endpoints. We may also explore for any potential confounders in VO_2peak_ within the study, and the complier averaged causal effect (CACE) analysis as a sensitivity analysis.

- 1. **Procedure(s) to account for missing or spurious data**

We will endeavour to collect all data possible from each participant during their enrolment in the study. Data monitoring will be carried out by the trial manager/researcher and any missing data points will be raised as a query on the online database which will be followed up by the delivery team. If it is judged that the same critical data points (as outlined in the data management plan) are consistently being missed (>10%) then this will be raised at the following TMG for corrective action.

Multiple imputation methods will be used as secondary analysis if more than 10% of the outcome variable is missing.

- 1. **Economic Evaluation**

To assess the costs, benefits, and overall cost-effectiveness of the intervention, we will integrate a prospective economic evaluation into the trial. The time horizon of the analysis will be one year, congruently with the duration of the trial. The primary perspective will be NHS and Personal Social Services (PSS), with secondary analyses including additional patient costs accruing over the 12 months period post ablation.

Resource use and costs

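### Holter length is given as 1–7 days in three places and 7 days in a fourth, and AF sampled in two Holter windows is to be analysed by Kaplan-Meier and time-to-event methods

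*Protocol*

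**What the plan says.** **Recording length.** The Protocol gives it in four places:

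| Place in Protocol | Length |
|---|---|
| Study Summary, secondary outcomes | "AF recurrence and burden from data collected from a 1–7-day(s) cardiac Holter monitoring at 10 weeks" |
| Schedule of Events, Table 1 | "1–7-day(s) Holter monitor" |
| Section 5, Objectives and Outcome Measures | "This will be assessed with a 1–7-day cardiac Holter monitor at 10 weeks (±2 weeks) and 12-months (±4 weeks) post ablation" |
| Section 9, Follow-up data | "7-day Holter ECG monitoring will be placed on patients at the 10 weeks and 12 months post-ablation follow-up appointments" |

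**What is taken from the recording.** Section 5 takes the AF event, the burden and the time of occurrence only over the period the monitor was worn.

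**What counts as a recurrence.** Section 9 (Follow-up data) counts AF captured on a 12-lead ECG, or AF lasting at least 30 seconds on ECG monitoring. The same paragraph equates the 10-week (±2 weeks) period with the usual 3-month blanking period, in which AF is not a recurrence.

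**Analysis.** Section 10 (Secondary outcome analysis) states: "Proportion of significant AF event by treatment arms will be estimated with associated 95% CI using Kaplan-Meier". It adds: "The recurrence of AF burden from the Holter and each of the MACE occurrence will also be estimated by treatment arms as a time-to-event estimand".

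**The concern.** There are two separate problems.

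The first is measurement. The chance of catching intermittent AF rises with hours recorded. A protocol that allows anything from one to seven days in three places and fixes seven in a fourth does not fix the sensitivity of the outcome. Recording length is a matter of trial conduct, so analysis wording written later cannot restore days that were never recorded.

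The second is the match between data and method. Kaplan-Meier assumes that the event time is known, or is known to lie beyond the last observation. A Holter fitted at a scheduled visit shows whether AF was present during that window. It does not show when AF returned. Burden, the amount of AF in the recording, is a quantity and has no event time at all.

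At stake is whether the trial's statement on AF recurrence after ablation can be interpreted: how many recurrences were missed, what the time axis of the curve means, and whether AF seen at 10 weeks counts.

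**Working it through.** The Protocol gives no event rate, power or sample size for AF recurrence, so it has no figure of its own to reproduce here.

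**1. Share of follow-up observed by Holter.** There are two recordings of 1 to 7 days each:
- both windows: 2/365 = 0.5% to 14/365 = 3.8%;
- if the 10-week recording is blanked, taking blanking to end at 12 weeks (day 84), 281 days remain and one window covers 1/281 = 0.4% to 7/281 = 2.5%.

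**2. Interval censoring.** Suppose a participant has no AF on the 10-week Holter and AF on the 12-month Holter. AF returned at some point between the two:
- nominal interval: 52 − 10 = 42 weeks;
- with the visit windows: from (52 − 4) − (10 + 2) = 36 weeks to (52 + 4) − (10 − 2) = 48 weeks.

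Kaplan-Meier on detection dates puts the whole step at the visit. Two participants with the same AF history can differ by up to 8 weeks in event time solely because of where their appointment fell within ±4 weeks. Section 5 does record when the episode occurred, but that dates an episode inside the recording, not the onset of recurrence.

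**3. Detection by recording length.** The episode rates below are assumptions; the Protocol gives none. With random episodes averaging one every *m* days, P(detect in *d* days) = 1 − exp(−*d*/*m*). For *m* = 7 this is 1 − exp(−1/7) = 13% for one day and 1 − exp(−7/7) = 63% for seven.

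| Assumed frequency | 1 day | 7 days |
|---|---|---|
| one per 3 days | 28% | 90% |
| one per 7 days | 13% | 63% |
| one per 14 days | 7% | 39% |
| one per 30 days | 3% | 21% |

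Continuous AF at recurrence would be seen on day one whatever the length, so the table applies to intermittent AF.

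**4. Equal wear in both arms.** Section 8 puts first-procedure success at about 40–80% at 1–2 years, so recurrence is roughly 20–60%. Taking 40% in both arms and one episode a week, observed recurrence is 0.40 × 0.133 = 5% with one day and 0.40 × 0.632 = 25% with seven. Both arms are multiplied by the same detection fraction. No difference appears where none exists, but most recurrences can be missed.

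**5. Unequal wear (hypothetical).** With mean wear of 5 days against 3 at one episode a week, detection is 51% against 35%, a gap of 16 points among patients who all have recurrent AF. Over a whole arm, multiply by the recurrence proportion: 0.161 × 0.2 = 3 points to 0.161 × 0.6 = 10 points. At 40% recurrence the observed proportions are 0.204 and 0.139. With the 44 per arm implied by the 88 in Section 10, SE ≈ √[(0.204×0.796 + 0.139×0.861)/44] = 0.080 and z ≈ 0.065/0.080 = 0.81. The chance of a false significant result is then about 12%, against a nominal 5%.

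**6. The 10-week recording.** The Study Summary draws AF recurrence from it. Section 9 treats that period as one in which AF is not a recurrence. Read literally, the two cannot both hold, and the second leaves one usable Holter window.

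**The case against.** **The lengths may be compatible.** Section 9 says what is placed, while Section 5 speaks of data over the time worn. A 7-day monitor could yield 1 to 7 days of data. This is a possible reading, but the Schedule of Events and Section 5 give 1–7 days as the monitor itself. The wording needs to be settled either way.

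**AF may be found outside the Holters.** Section 9 admits a 12-lead ECG. Section 5 adds a review of medical records at 12 months, although the Study Summary ties that review to redo ablation. Some AF may therefore carry a clinical date, and a time-to-event summary of such events has a basis. This part stands. It does not supply onset times for AF found only on a Holter.

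**Much of this is SAP detail.** Minimum wear, handling of wear time and censoring rules are commonly left to the SAP, and their absence here is no fault. However, Section 10 (Statistical Considerations) says the SAP will elaborate the analyses the Protocol describes, and Kaplan-Meier and the time-to-event estimand are already named. Recurrence of burden may simply be loose wording for recurrence of AF on the Holter; if so, it should say that.

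**A reader might infer that the arm comparison is biased.** The documents do not support this. Both arms have the same Holter at the same two visits, and nothing states or implies different wear. Participants know their allocation, and the stated blinding covers only the follow-up exercise physiologists. A difference in wear is therefore possible, but it is not shown.

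**Conclusion.** The point holds in limited form. The Protocol contradicts itself on Holter length. It names Kaplan-Meier and time-to-event analysis for Holter AF that is interval-censored over roughly 36 to 48 weeks, and for burden, which is not an event. It also leaves unclear whether AF on the 10-week recording is a recurrence.

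With equal wear the cost is missed recurrences, lost precision and event times that largely reflect the appointment schedule. The detection figures (13% against 63% at one episode a week; 3% against 21% up to 28% against 90% across the range) rest on assumed random episodes and do not apply to continuous AF. The 16-point gap should not be read as an expected bias between arms: it needs an invented difference in wear and applies only to patients with recurrent AF. It is also too strong to say that Kaplan-Meier has no place, since clinically dated AF can be analysed that way.

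This is an exploratory, unpowered secondary outcome. The primary VO2peak analysis is unaffected.

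**What to change.** 1. Reconcile the Study Summary, the Schedule of Events, Section 5 and Section 9 to one intended recording length for all participants at both visits, and record analysable hours. The documents do not show which length was meant; the sponsor should decide.
2. Reconcile the 10-week recurrence outcome with the blanking statement, so that it is clear whether AF on that recording is a recurrence or is reported separately.
3. In Section 10, analyse Holter-detected AF as a binary outcome in each scheduled window (risk difference between arms with 95% CI), or use an interval-censored method. Analyse burden as percent of analysable time.
4. Keep Kaplan-Meier for events with a date: MACE, redo ablation and clinically documented AF.
5. Report wear time by arm. Use any adjustment for wear, or restriction to near-complete recordings, only as a sensitivity analysis. Wear is measured after randomisation, so conditioning on it in the main analysis could itself bias the comparison.

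The cost is Protocol wording with matching SAP text and, if the longer end of the range is chosen, longer wear for some participants. Some recordings will still fall short, and reporting wear by arm makes that visible without removing it.

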# **STUDY FLOW CHART**

*Figure 1: Flow of participants through the study*

[figure not shown]

# **SCHEDULE OF EVENTS**

*Table 1: Schedule of Events*

| **Procedure** | **Pre-Screening/ Lead-In Period** | **Consent & Baseline** | **Pre-Ablation Intervention** | **AF Ablation Procedure*** | **Rest** | **Post-Ablation Intervention** | **Follow-Up & Outcome Measure** | **Follow-Up** |
| --- | --- | --- | --- | --- | --- | --- | --- | --- |
|  | **Month -4 to Month -1** | **Week -2 to Day 1** | **Up to Week 8** | **Week 9 (Day 1 Ablation)** | **Up to Week 11 (2 weeks post-ablation)** | **Up to Week 19 (Up to week 10 post-ablation)** | **Up to Week 21 (Up to week 12 post-ablation)** | **Month 12 (±4weeks) post ablation** |
| Screening | X |  |  |  |  |  |  |  |
| Eligibility assessment | X |  |  |  |  |  |  |  |
| Re-Confirm Eligibility |  | X |  |  |  |  |  |  |
| Informed consent |  | X |  |  |  |  |  |  |
| Questionnaire completion (EQ-5D, SF-36, AFEQT) |  | X |  | X |  |  | X | X |
| Resource Use Questionnaire |  |  |  | X |  |  | X | X |
| Demographic data (Year of birth, sex, ethnicity, height, and weight) |  | X |  |  |  |  |  |  |
| Smoking and diet history |  | X |  |  |  |  |  |  |
| Relevant clinical history |  | X |  |  |  |  |  |  |
| Current medications |  | X |  |  |  |  |  |  |
| Standard blood tests* |  | X |  |  |  |  |  |  |
| Cardiopulmonary exercise testing |  | X |  |  |  |  | X |  |
| Randomisation |  | X |  |  |  |  |  |  |
| 1-to-1 behavioural & motivational education sessions |  |  | X^1^ |  |  | X^1^ |  |  |
| 30-minute AF risk factor modification education session |  |  | X^2^ |  |  |  |  |  |
| AF Ablation* |  |  |  | X |  |  |  |  |
| Cardiopulmonary exercise sessions for intervention arm |  |  | X |  |  | X |  |  |
| Adverse Event Reporting |  | X | X | X | X | X | X | X |
| 1–7-day(s) Holter monitor |  |  |  |  |  |  | X | X |
| Primary Outcome Analysis |  |  |  |  |  |  | X |  |
| Review of hospital records (MACE, need for redo-AF ablation, etc.) |  |  |  |  |  |  |  | X |

** Part of Standard Care*

*X^1^ 1-to-1 behavioural & motivational education session alternating weeks for 6-8 weeks pre- and post-ablation only occurring in the intervention arm*

*X^2^ one off 30-minute education session activity only occurring in the control arm*

# **LIST OF ABBREVIATIONS**

| AE | Adverse Event |
| --- | --- |
| AR | Adverse Reaction |
| AF | Atrial Fibrillation |
| AFEQT | Atrial Fibrillation Effect on Quality of Life |
| BP | Blood Pressure |
| CI | Chief Investigator |
| CPET | Cardiopulmonary Exercise Test |
| CRF | Case Report Form |
| ECG | Electrocardiogram |
| EDC | Electronic Data Capture |
| GCP | Good Clinical Practice |
| ICF | Informed Consent Form |
| ISF | Investigator Site File |
| MACE | Major Adverse Cardiovascular Events |
| MCS | Mental Component Summary |
| NICE | National Institute for Clinical Excellence |
| PCS | Physical Component Summary |
| PI | Principal Investigator |
| PIS | Participant Information Sheet |
| PVI | Pulmonary Vein Isolation |
| QALY | Quality Adjusted Life Year |
| QoL | Quality of Life |
| RCT | Randomised Control Trial |
| REC | Research Ethics Committee |
| RU | Resource Use |
| SAE | Serious Adverse Event |
| SAR | Serious Adverse Reaction |
| SDV | Source Data Verification |
| SOP | Standard Operating Procedure |
| SUSAR | Suspected Unexpected Serious Adverse Reaction |
| TMF | Trial Master File |
| TMG | Trial Management Group |
| UHCW | University Hospitals Coventry & Warwickshire |
| VAS | Visual Analogue Scale |

